### **3.5 Final report**

A summary will be issued within four weeks of study completion and a final report within 4 weeks of sponsor's comments. This report should include number of subjects enrolled, number of subjects dropped/withdrawn, deviations, amendments, statistical analysis and general or specific comments from the investigator. Additionally, the contract laboratory will provide the sponsor/study co-ordinator with the electronic data.

### **3.6 Insurance**

In the unlikely event of any subject suffering any significant deterioration in health or wellbeing arising as a result of taking part in this study, Unilever has undertaken to compensate them without having to prove that anyone involved in this study has been negligent. Any dispute will be referred to an arbitrator.

---

## **APPENDIX 8 – Educational Information**

## **APPENDIX 1 - Study Schedule**

| Phases                                                           | Processes                                                                                                                                          |
|-------------------------------------------------------------------------|-----------------------------------------------------------------------------------------------------------------------------------------------------------|
| Time 1:

Recruitment/Screening
(Virtual Surveys) | -Screening questionnaire (height, weight, health status, age, gender, cholesterol and healthy eating motivation).

-Online signing of consent form. |

|                                                                                     |                                                                                                                                                                                 |
|-------------------------------------------------------------------------------------|---------------------------------------------------------------------------------------------------------------------------------------------------------------------------------|
| Conduction of Intervention                                                   | -Allocation to different experimental conditions.

-Questionnaire assessing subject's intentions, saturated fat intake, self-efficacy, planning etc.                      |
| Duration                                                                     | 30mins                                                                                                                                                                          |
| Time 2
Post-Study Assessment

Payment of participants | -Follow-up questionnaire assessing subject's reactions, self-efficacy, planning, saturated fat intake, intentions.

-Subjects directed back to Virtual Surveys to be paid |
| Duration                                                                     | 30mins                                                                                                                                                                          |

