| Study Objective (s)             | The aim of the study is to investigate the role of Planning and SMS reminders in the promotion of a more balanced diet.                                                                                                                                                                                                                                                                                                                                                                                                     |
| Study Design                    | Randomised Control Trial                                                                                                                                                                                                                                                                                                                                                                                                                                                                                                    |
| Study Population
Sample Size | 750 UK online users will be recruited, women and men between the ages of 30-60.                                                                                                                                                                                                                                                                                                                                                                                                                                             |
| Intervention                    | An Internet based study. Volunteers will be allocated into one of three different conditions: a) Control Group, b) Planning (=Implementation Intentions) and c) Planning and Short Message Service (SMS) Reminders. At Time 1, all subjects will be asked to fill out a set of questionnaires and then will be allocated into one of these three conditions. Four weeks later, subjects will come back to the website and report on changes in healthy eating, saturated fat intake and various psychological determinants. |

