### Part I: Study Schematic:

| Phase 1                        | Phase 2                                                                                                                                             |
|--------------------------------|-----------------------------------------------------------------------------------------------------------------------------------------------------|
| 1) Subjects' Online Screening  | 1) Filling out Questionnaires on:

a) Saturated Fat Intake

b) Social Cognitive Determinants

c) Feedback on Information Received |
| 2) Signing Online Consent Form |                                                                                                                                                     |
| 3) Filling out Questionnaires  |                                                                                                                                                     |

|                                                                                                                                                          |                                                                                                                                                   |
|----------------------------------------------------------------------------------------------------------------------------------------------------------|---------------------------------------------------------------------------------------------------------------------------------------------------|
| 4) Random allocation of subjects in one of three conditions:
a) Control Group
b) Planning
c) Planning and Short-Message Service (SMS) Reminders |                                                                                                                                                   |
| 6) Re-direction to Virtual Surveys' website                                                                                                              | 2) Re-direction to Virtual Surveys' website

3) Payment of Subjects (stage 1: £5; stage 2: £10; payment received upon completion of Stage2) |

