## 1.3 Brief Description of Intervention

To the best of our knowledge there are no studies that have tested online the combined effects of planning with SMS reminders in a more complex behaviour such as dietary changes. In the present study, the aim was to test for differences on the effects of three different conditions on saturated fat intake and the purchase of products that contribute to lowering or helping maintain a healthy diet.

At **Time 1**, subjects will be invited to participate in the study by an online recruitment agency, which will also carry out the screening process. Once, subjects have been accepted in the study they will be randomly allocated into one of three conditions. In the most advanced condition, subjects will be asked to form implementation intentions and be reminded of their plans by SMS reminders over the course of the two weeks. In the second condition, they will be asked to form plans on how to eat healthier over the course of two weeks. All conditions will be asked to fill out questionnaires on: a) a self-reported dietary intake questionnaire (Margetts et al, 1989) and b) a self-reported questionnaire on various social cognitive variables (e.g. intentions, self-efficacy). The Control Group (CG) will be only asked to fill out these questionnaires at this stage. All three groups will receive educational information on the importance of a healthy diet low in saturated fat and the association between high cholesterol and being overweight. A coupon of a cholesterol lowering product, with 50p off the face value, will be posted to all participants as a reward for successfully completing baseline assessments.

At **Time 2 (4 weeks later)**, subjects will be invited to fill out again the same dietary measures of food intake and an extension of the psychological determinants' questionnaire. Study subjects will be rewarded for their participation in the study (£15). This will be upon completion of study phase 2.

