### a) Recruitment and Screening

Recruitment will be conducted by Virtual Surveys (<http://www.virtualsurveys.com/s>), an online recruitment agency, to cost effectively reach a specific target sample within the UK population. Virtual Surveys have their own online panel and a structured script will be used to screen individuals and exclude any people who do not meet the inclusion criteria (Appendix 5). Once subjects meet the inclusion criteria, they will be acquainted with the study procedures and asked to read an online informed consent form. They will be requested to click on a number of check boxes to make sure they have read and understood the information before they proceed to the online questionnaires. There will be two types of questionnaires at this phase: a) food frequency questionnaire and b) questionnaire focusing on social-cognitive determinants.

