### b) Intervention

In the main study phase, subjects will be randomly allocated into one of three different conditions: a) Control Group, b) Planning and c) Planning and SMS Reminders. Subjects in the experimental conditions will be first provided with information on a healthy diet, the importance of good fats in a person's diet and the link between cholesterol, diet and overweight.

Subjects in the planning condition will then identify a list of situations where they would like to change their dietary intake. They will then be asked to match these situations with a list of behaviours. They would be requested to choose pairs of situations and behaviours that they want

to change rather than ones that they are already doing (Appendix 4). The list of behaviours is based on the process of change model of Prochaska (1979). It includes strategies such as counterconditioning, stimulus control and use of helping relationships. A number of more nutritionally based behaviours have also been created with the help of an expert nutritionist and information from accredited sources such as the Food Standard's Agency 'eat well, be well' site (<http://www.eatwell.gov.uk/>). Once, they have made their selections they will be given the option to go back to improve their plan or revise their situation-solutions.

Subjects in the SMS reminders and planning condition will also follow the same process to choose their situation-solution pairs and then be provided with SMS reminders of these pairs over the course of the 4 weeks. Two SMS reminders will be sent per week. Subjects will be able to choose the time of the day they would like to receive the SMS reminder. Subjects will be also informed that use of their mobile number for the SMS reminders will be made only during the duration of the study and they will not be contacted any further upon completion of the study.

All subjects will be invited to answer a number of questions on their perceptions of the information received, intentions to make lifestyle changes, feelings of self-efficacy. Subjects in the control group will be told that they will be put on a waiting list and will receive further information in four weeks time.

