### **11.2 Data Analysis and Plan of Efficacy**

A full statistical analysis plan will be formulated in collaboration with [name] from the Unilever Statistics Group, Colworth Park. The effect of the design factors will be determined by comparing the proportion of subjects who have reduced their self-perceived saturated fat intake. Analysis of variance with baseline covariates will be conducted to analyse the behavioural (TIS, FFQ, portion sizes changes, other health behaviours) and social-cognitive measures (intentions, self-efficacy, planning, feedback). Baseline self-reported saturated fat intake will be included as a covariate for the analysis of the primary outcome measures. The stratification variables will be included in the models as will other covariates found significant at the 0.05 level. Comparisons between treatments will all be reported using two-sided significance levels (i.e. making no prior assumption about which treatment group will be most effective). Separate analysis of the effects of modifiers and mediators will be conducted in order to gain a better insight as to who benefits from the intervention.

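### The protocol contradicts itself on whether Time 1 questionnaires precede allocation, so Stage 1 intentions, self-efficacy and coping planning may be post-intervention values used as baseline covariates

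*Protocol*

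**What the plan says.** Three places put the Time 1 questionnaires before allocation:

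- Protocol Summary, Intervention: "all subjects will be asked to fill out a set of questionnaires and then will be allocated into one of these three conditions".
- Study Schematic: questionnaires are step 3, followed by "4) Random allocation of subjects in one of three conditions".
- Section 5.1 a), after consent and before the part headed Intervention: "There will be two types of questionnaires at this phase: a) food frequency questionnaire and b) questionnaire focusing on social-cognitive determinants".

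Two places suggest another order:

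- Appendix 1, Time 1, in the cell for conducting the intervention: the first item is "Allocation to different experimental conditions" and the second is "Questionnaire assessing subject's intentions, saturated fat intake, self-efficacy, planning etc".
- Section 1.3, more loosely: "Once, subjects have been accepted in the study they will be randomly allocated into one of three conditions". The arms come next, and only then the questionnaires.

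Section 5.1 b), after describing the information, the planning task and the SMS set-up, says all subjects answer "questions on their perceptions of the information received, intentions to make lifestyle changes, feelings of self-efficacy".

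In Appendix 3, intentions, maintenance and recovery self-efficacy, and coping planning are marked for Stages 1 and 2. Each has one form, with no split of Stage 1 into before and after the intervention. Action planning and the feedback items are marked Stage 2 only.

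Section 11.2 states: "Analysis of variance with baseline covariates will be conducted to analyse the behavioural" and social-cognitive measures. It names baseline saturated fat intake as a covariate for the primary outcomes, and adds the stratification variables and any other covariate significant at the 0.05 level.

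**The concern.** A baseline covariate is safe to adjust for because the intervention cannot have affected it. If Stage 1 intentions, self-efficacy or coping planning are answered after a subject has read the material or built three if-then plans, they already carry part of the effect. Adjusting for them then removes that part. Coping planning is the clearest case: it asks whether the subject has a detailed plan, possibly minutes after the subject has made one.

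The values could enter in two ways: as the baseline for the same scale at Time 2, or as a covariate that passes the 0.05 screen in a model for another outcome, where it would act as a mediator. The mediation objective in section 2.2 also needs a known time order. The separate analysis plan can restrict covariates, but it cannot recover a pre-intervention answer that was never collected.

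**Working it through.** **1. Order at Time 1, side by side**

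| Source | Order | How firm |
|---|---|---|
| Protocol Summary | Questionnaires, then allocation | Explicit |
| Study Schematic | Step 3, then step 4 | Numbered |
| 5.1 a) and b) | Both questionnaires in a), allocation in b) | By section |
| Appendix 1 | Allocation, then questionnaire | Unnumbered bullets in one cell |
| 1.3 | Allocation described before questionnaires | Loose narrative |
| 5.1 b) | Intentions and self-efficacy after the task | By position in the text |

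With one Stage 1 form per scale, the protocol does not say whether the 5.1 b) items are that form or an additional measurement.

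**2. The plan's own figure**

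Section 11.3 gives about 180 respondents for power 0.8 at two-sided 0.05. It gives no effect size or SD and does not say whether 180 is per arm or in total, so the figure cannot be reproduced. It can only be solved backwards, with d = (1.960 + 0.842) × √(2/n):

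- 180 per arm: d = 0.295.
- 180 in total, 90 per arm: d = 0.418.

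**3. Effect of adjusting for a post-intervention covariate**

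Let b be the within-arm slope on the covariate and f the share of the Time 2 effect already present in the Time 1 answer. The adjusted effect is the true effect × (1 − b·f).

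Inputs: b = 0.61 is an assumption, borrowed from the food frequency questionnaire's test-retest correlation in section 5.2. It does not belong to the social-cognitive scales. The share f is not in the protocol. Power starts from the stated 0.80, so power = Φ(2.802 × (1 − b·f) − 1.960) under either reading of 180.

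| f | Effect kept (b = 0.61) | Power |
|---|---|---|
| 0 | 1.00 | 0.80 |
| 0.25 | 0.85 | 0.66 |
| 0.5 | 0.70 | 0.50 |
| 1 | 0.39 | 0.19 |

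Example, f = 0.5: 1 − 0.61 × 0.5 = 0.695, and Φ(2.802 × 0.695 − 1.960) = Φ(−0.01) = 0.50.

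A simulation with 3,000 runs per value of f (n = 180 per arm, b = 0.61) gave 1.00, 0.86, 0.69 and 0.39 kept, with power 0.79, 0.66, 0.50 and 0.19. Over b = 0.3 to 0.8, f = 0.5 keeps 85% to 60% (power 0.66 to 0.39).

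The power column is calibrated to section 11.3, which concerns self-perceived saturated fat intake, so it shows scale only. It is not a forecast for that endpoint or for the other scales.

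**4. Where f could be material**

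- Intentions, self-efficacy, coping planning: they describe the subject's current state, so a shift within the session is plausible.
- Saturated fat intake: the food frequency questionnaire covers the previous month and the two-item measure the last four weeks. A task minutes earlier cannot change past intake; only reporting could shift. Section 5.1 b) does not list these items after the task.
- Planning versus Planning with SMS: both arms go through the same planning process at Time 1, so a post-task value should be similar between them in expectation. The bias concerns mainly comparisons with control.

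**The case against.** Every place that fixes an order explicitly puts the questionnaires first. Appendix 1 is an unnumbered list that mentions neither the education nor the planning task, and allocation alone changes no answers. Section 1.3 has no sequence words between the arms and the questionnaires, and it calls the Time 1 measures baseline assessments. The 5.1 b) items may be extra questions, since 5.1 a) already includes a social-cognitive questionnaire and the wording of 5.1 b) is broader than the intentions scale in Appendix 3. Section 11.2 names only saturated fat intake as a questionnaire covariate and leaves detail to a full analysis plan.

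Most of this stands, and it rules out treating a post-intervention baseline as settled. It does not remove the conflict. Appendix 3 gives no second Stage 1 form for the 5.1 b) items, and the covariate rule in 11.2 is open to any significant variable whenever it was measured.

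A reader might go further and infer that the primary saturated fat effect is adjusted away, with power falling to about 0.19. The documents do not support that. It needs full carry-over (f = 1) into items about past intake, which is implausible. Even the direction is uncertain: learning which foods contain bad fats could raise reported intake at Time 1, and adjustment would then enlarge the apparent reduction.

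**Conclusion.** The contradiction is real and should be resolved before launch. It leaves open whether Stage 1 intentions, self-efficacy and coping planning are pre- or post-intervention values, and section 11.2 does not keep the latter out of the models. At stake are the social-cognitive comparisons with control, the mediation analysis, and any primary model that takes in one of these scales through the 0.05 screen. The direct risk to the primary outcome through its own saturated fat baseline is probably small.

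The size cannot be fixed from the protocol. The loss is b·f of the effect; with the assumed b = 0.61 it is about 15% at f = 0.25 and 30% at f = 0.5. The 61% loss at f = 1 is the far end of the range shown, not an estimate.

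**What to change.** 1. Align Appendix 1 with the Protocol Summary, the Study Schematic and section 5.1 a), and clarify section 1.3: the food frequency questionnaire, two-item measure, intentions, self-efficacy and coping planning are completed and locked before allocation is revealed.
2. In section 5.1 b) and Appendix 3, label the questions after the task as a separate 'Time 1 post-intervention' measure. They may serve as early mediator measures, never as baseline covariates.
3. In section 11.2, restrict covariates to values measured before allocation, including any chosen by the 0.05 rule.

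The cost is page order in the online system and wording in a few sections, plus about a minute per subject if intentions and self-efficacy are asked both before and after the task. It cannot be repaired once data are collected.

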## APPENDIX 3 – QUESTIONNAIRES

Self-Report Index of Food (Margetts et al, 1989): Stage 1/2

This questionnaire will be presented to subjects with the title 'Eating Habits'

Please choose the frequency with which you have eaten each of the foods in the list below.

| Food                        | 2 or more times per day | Every day | Three to five times per week | One to two times per week | One to three times per month | Rarely or never |
|-----------------------------|-------------------------|-----------|------------------------------|---------------------------|------------------------------|-----------------|
| Whole milk                  |                         |           |                              |                           |                              |                 |
| Semi-skimmed milk           |                         |           |                              |                           |                              |                 |
| Skimmed milk                |                         |           |                              |                           |                              |                 |
| Butter                      |                         |           |                              |                           |                              |                 |
| Margarine                   |                         |           |                              |                           |                              |                 |
| Polyunsaturated margarine   |                         |           |                              |                           |                              |                 |
| Low fat spread              |                         |           |                              |                           |                              |                 |
| Ice cream                   |                         |           |                              |                           |                              |                 |
| Yoghurt                     |                         |           |                              |                           |                              |                 |
| Cheese- ordinary            |                         |           |                              |                           |                              |                 |
| Cheese- low fat             |                         |           |                              |                           |                              |                 |
| Eggs- fried                 |                         |           |                              |                           |                              |                 |
| Eggs- not fried             |                         |           |                              |                           |                              |                 |
| Cheese/egg meals            |                         |           |                              |                           |                              |                 |
| Beef- roast/steak           |                         |           |                              |                           |                              |                 |
| Lamb- roast/chops           |                         |           |                              |                           |                              |                 |
| Pork- roast/chops           |                         |           |                              |                           |                              |                 |
| Chicken/Turkey              |                         |           |                              |                           |                              |                 |
| Bacon                       |                         |           |                              |                           |                              |                 |
| Meat dishes                 |                         |           |                              |                           |                              |                 |
| Canned meats                |                         |           |                              |                           |                              |                 |
| Meat pies/pasties           |                         |           |                              |                           |                              |                 |
| Sausages/beefburgers        |                         |           |                              |                           |                              |                 |
| Liver/Kidney/Pate           |                         |           |                              |                           |                              |                 |
| Fish- not fried             |                         |           |                              |                           |                              |                 |
| Fish-fried                  |                         |           |                              |                           |                              |                 |
| Fish-canned                 |                         |           |                              |                           |                              |                 |
| Bread-white                 |                         |           |                              |                           |                              |                 |
| Bread-brown/granary         |                         |           |                              |                           |                              |                 |
| Bread-wholemeal             |                         |           |                              |                           |                              |                 |
| Sweet biscuits              |                         |           |                              |                           |                              |                 |
| Crackers/crispbread         |                         |           |                              |                           |                              |                 |
| Cakes/buns/pastries         |                         |           |                              |                           |                              |                 |
| Puddings                    |                         |           |                              |                           |                              |                 |
| Breakfast Cereal-High fibre |                         |           |                              |                           |                              |                 |
| Breakfast Cereal- Ordinary  |                         |           |                              |                           |                              |                 |
| Breakfast Cereal- Muesli    |                         |           |                              |                           |                              |                 |
| Rice/Pasta                  |                         |           |                              |                           |                              |                 |
| Apples/Pears                |                         |           |                              |                           |                              |                 |

|                     |  |  |  |  |  |  |
|---------------------|--|--|--|--|--|--|
| Oranges/Grapefruits |  |  |  |  |  |  |
| Bananas             |  |  |  |  |  |  |
| Green Vegetables    |  |  |  |  |  |  |
| Carrots/Tomatoes    |  |  |  |  |  |  |

| Food                            | 2 or more times per day | Every day | Three to five times per week | One to two times per week | One to three times per month | Rarely or never |
|---------------------------------|-------------------------|-----------|------------------------------|---------------------------|------------------------------|-----------------|
| Other Vegetables                |                         |           |                              |                           |                              |                 |
| Baked beans                     |                         |           |                              |                           |                              |                 |
| Other beans/lentils             |                         |           |                              |                           |                              |                 |
| Vegetable dishes                |                         |           |                              |                           |                              |                 |
| Potatoes- fried                 |                         |           |                              |                           |                              |                 |
| Potatoes- not fried             |                         |           |                              |                           |                              |                 |
| Beer/lager                      |                         |           |                              |                           |                              |                 |
| Wine/sherry/spirits             |                         |           |                              |                           |                              |                 |
| Tea/Coffee                      |                         |           |                              |                           |                              |                 |
| Squash/Fizzy drinks             |                         |           |                              |                           |                              |                 |
| Low calorie drinks              |                         |           |                              |                           |                              |                 |
| Pure fruit drinks               |                         |           |                              |                           |                              |                 |
| Chocolate                       |                         |           |                              |                           |                              |                 |
| Sweets                          |                         |           |                              |                           |                              |                 |
| Sweet spreads                   |                         |           |                              |                           |                              |                 |
| Sugar                           |                         |           |                              |                           |                              |                 |
| Crisps and other savoury snacks |                         |           |                              |                           |                              |                 |
| Nuts (including peanut butter)  |                         |           |                              |                           |                              |                 |
| Sauces and pickles              |                         |           |                              |                           |                              |                 |
| Salad oil/ dressing/mayonnaise  |                         |           |                              |                           |                              |                 |

